In case an adjustment disorder is diagnosed, evidence or practice based psychological interventions should be available and provided to the patient [3]. However, in clinical practice, psychological treatment is often not optimally accessible for cancer patients, especially for those with an adjustment disorder. Several bottlenecks in the organization of psychological treatment have been identified, including problems with identifying cancer patients with an adjustment disorder, and problems with referral to psychological treatment [9–13]. In addition, when an adjustment disorder is diagnosed in cancer patients, the accessibility of psychological care is limited, since there is currently no adequate coverage and reimbursement of adjustment disorders treatments in cancer patients after active cancer treatment [14].

A systematic review of Faller et al. (2013) [15] and several studies published after the conduction of this review [16–24] showed evidence for the effectiveness of psychological interventions targeting cancer patients, including self-management interventions, eHealth interventions, group interventions, and individual interventions. Also, two reviews showed that psychological interventions targeting cancer patients are likely to be cost-effective at potentially acceptable willingness-to-pay thresholds [25, 26]. Three recent cost-utility studies, on meaning-centred group psychotherapy, stepped psychological care, and blended cognitive behavioural therapy, even showed that psychological treatment is more effective and potentially less costly compared to care-as-usual [16, 27, 28]. However, to the best of our knowledge, no study specifically focused on the effectiveness, cost-utility and budget impact of psychological interventions in cancer patients with an adjustment disorder.

This randomized controlled trial, therefore, aims to provide insight into the prevalence of an adjustment disorder among cancer patients, and the reach, effectiveness, cost-utility and budget impact of a tailored psychological intervention. The results are relevant to improve care (including accessibility and reimbursement) for cancer patients with an adjustment disorder.

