### Sample size

The sample sizes of Part 1 and 2 depend on each other. To demonstrate an effect size in Part 2 of 5 points on the HADS as statistically significant, anticipating a standard deviation of 11 (i.e. two times the baseline standard deviation of the HADS), 77 participants in each condition are needed at follow-up (power 80%, significance level 5%). Anticipating a drop-out rate of 25% between baseline and 6 month follow-up, 103 participants per condition, thus 206 in total, need to be included at baseline. Estimating a willingness to participate in this RCT of 60%, 343 patients will need to be approached to participate in the RCT in Part 2 [49]. Taking into account a prevalence rate of adjustment disorders of 11% as estimated by Mehnert et al. [7], 3119 cancer patients need to be screened in Part 1 to identify 343 patients with adjustment disorders. Anticipating a response rate of 50%, 6238 patients need to be approached for the screening.

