For the cost-utility analyses, pertinent guidelines will be used [44]. Analyses will be conducted in agreement with the intention-to-treat principle from both a societal and healthcare perspective. Costs will be calculated by multiplying resource use by integral cost prices as presented in the cost guideline [44]. Productivity losses due to absenteeism and presenteeism will be calculated using the friction cost approach. Missing data on costs and utilities will be imputed using multiple imputation. The time horizon will be set at 6 months, and therefore neither costs nor effects need to be discounted. Incremental cost-utility ratios (ICURs) will be calculated with their 95% confidence intervals using 5000 bootstrap replications, which will be projected on a cost-utility plane. In addition, ICUR acceptability curves will be presented and sensitivity analyses will be performed focusing on uncertainty surrounding most important cost items.

For the budget impact analyses, the current guideline on budget impact analyses of the Dutch National health Care Institute (ZIN) and the International Society for Pharmacoeconomic and Outcomes Research will be used [44, 50]. To perform a budget impact analysis insight is needed on: a) size of the target population, b) costs of the intervention and 3) other costs (such as other healthcare costs). Several budget impact analyses will be performed, as this will provide insight into the uncertainty surrounding the budget impact of providing psychological treatment to patients with cancer with an adjustment disorder. Budget impact analyses will be performed from a healthcare (i.e. including intervention costs and healthcare costs), societal (i.e. including intervention costs, healthcare costs, costs of the patient and his/her family and costs in other sectors) and insurer perspective (i.e. including costs reimbursed by the healthcare insurance company).

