
The second part of this project aims to investigate the effectiveness, cost-utility and budget impact of the tailored psychological intervention. It is expected that this psychological intervention will be especially effective, since the intervention is tailored to the individual needs regarding intensity of the intervention (i.e. number of modules provided) and wishes regarding the type of intervention. Besides being effective, it is hypothesized that offering this intervention will be cost-effective and potentially even cost-saving.

The cost saving potential is related to the design of the study in which patients are first provided with the short psychological treatment (module 1). The following modules (i.e. module 2 and 3) will only be offered to the patient if the previous psychological treatment module is insufficiently effective. This principle is comparable to a previously investigated stepped care intervention targeting head and neck cancer and lung cancer patients with psychological distress which was shown to be more effective and less costly compared to usual care [17, 27].

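### The 95% bootstrap interval for the ICUR is promised in all cases, but it misleads if replicates spread over several quadrants, a result the protocol leaves open

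*Protocol article*

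**What the plan says.** The Statistical analysis section of the protocol article fixes the main cost-utility summary: "Incremental cost-utility ratios (ICURs) will be calculated with their 95% confidence intervals using 5000 bootstrap replications, which will be projected on a cost-utility plane". It continues: "In addition, ICUR acceptability curves will be presented and sensitivity analyses will be performed focusing on uncertainty surrounding most important cost items". The horizon is short: "The time horizon will be set at 6 months, and therefore neither costs nor effects need to be discounted".

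On the expected result, the Discussion says that "it is hypothesized that offering this intervention will be cost-effective and potentially even cost-saving", and it likens the design to a stepped-care programme reported as both better and cheaper than usual care. The Background cites three cost-utility studies that "even showed that psychological treatment is more effective and potentially less costly compared to care-as-usual".

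The Sample size section concerns distress only: "To demonstrate an effect size in Part 2 of 5 points on the HADS as statistically significant". It arrives at 77 per arm at follow-up and 103 per arm at baseline. No cost or QALY difference, standard deviation or willingness-to-pay value is given.

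**The concern.** The ICUR is the cost difference divided by the QALY difference, and its sign does not identify the conclusion. A negative ratio means dominance in the south-east quadrant (more QALYs, lower cost) and the reverse in the north-west. A positive ratio has opposite decision rules in the north-east and south-west. As the QALY difference passes through zero, the ratio jumps between very large negative and very large positive values. An interval on the ratio therefore has a consistent meaning only when essentially all replicates lie in one trade-off quadrant with the QALY difference clearly away from zero.

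The plan promises the interval whatever the data show. Its own text treats a more effective and less costly result as possible, the horizon limits how large a QALY difference can become, and the sample size was not chosen to separate that difference from zero. The study was requested to inform a reimbursement decision (Implementation and clinical practice), and an ICUR with its interval is a figure that readers are likely to quote on its own.

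**Working it through.** **The plan's own figures.** None is stated for the ICUR, so the only inputs taken from the document are the group sizes. These reproduce. With a difference of 5, SD 11, two-sided 5% and 80% power, n = 2 × (1.960 + 0.842)² × (11/5)² = 76 per arm by the normal approximation, against 77 stated. Allowing for drop-out, 77/0.75 = 102.7, so 103.

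**Sign and ordering.** Net monetary benefit is NMB = λ × ΔQALY − Δcost, here with an illustrative λ of 20,000 euro per QALY.

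| ΔQALY | Δcost | ICUR | NMB |
|---|---|---|---|
| +0.02 | −500 | −25,000 | +900 |
| −0.02 | +500 | −25,000 | −900 |
| +0.02 | +500 | +25,000 | −100 |
| −0.02 | −500 | +25,000 | +100 |
| +0.01 | −500 | −50,000 | +700 |
| +0.05 | −500 | −10,000 | +1,500 |

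In each of the first two pairs, one ratio stands for opposite conclusions. In the last pair the result improves while the ratio moves towards zero, so the ratio does not order results even inside the cost-saving quadrant. This part needs no assumption about the data.

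**Illustration with assumed inputs.** Assume ΔQALY 0.02 (SD 0.08), Δcost −300 (SD 5,000), correlation −0.2 and 103 per arm.

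- Standard errors: 0.08 × √(2/103) = 0.0111 QALY and 5,000 × √(2/103) = 697 euro.
- Share of replicates with a negative QALY difference: Φ(−0.02/0.01115) = 3.6%.
- 5000 bivariate-normal replicates: 65% south-east, 31% north-east, 2% south-west, 2% north-west.
- ICUR: −300/0.02 = −15,000. The percentile 95% interval is about −166,000 to +159,000. A second set of 5000 gave about −189,000 to +152,000, so the limits themselves are unstable.
- NMB at λ = 20,000: mean 400 + 300 = 700. With 20,000 × 0.01115 = 223, its standard error is √(223² + 697² + 2 × 0.2 × 223 × 697) = 773. The 95% interval is 700 ± 1.96 × 773, or about −815 to +2,215, and P(NMB > 0) is about 0.82.

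**Range.** Thirty-six settings were run: ΔQALY 0.01, 0.02 or 0.03; Δcost −1,000, −300 or +500; SDs of 0.08 with 5,000 or 0.10 with 8,000; 77 or 103 per arm. All had replicates in at least three quadrants and an ICUR interval running from negative to positive. At the wide end, ΔQALY 0.01 and Δcost −1,000 (SDs 0.08 and 5,000, 103 per arm) gave about −1,056,000 to +874,000. At the narrow end, ΔQALY 0.03 and Δcost −300 with the same SDs and group size gave about −68,000 to +58,000.

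**Where the interval works.** With ΔQALY 0.04 (standard error 0.012) and Δcost +1,500 (standard error 700), about 98% of replicates are north-east and the interval is about 2,900 to 110,600. With ΔQALY 0.05 and Δcost +3,000 (SDs 0.08 and 5,000, 103 per arm), all are north-east and it is about 28,500 to 125,700. With Δcost −3,000 instead, all are south-east and it is finite, about −109,000 to −32,000, but still not ordered by value.

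**The case against.** The strongest reply is that the plan does not rely on the interval alone. The replicates are to be shown on a cost-utility plane, which displays the quadrants. The acceptability curve is the probability of positive net benefit across willingness-to-pay values, so it ranks results correctly; the 0.82 above is a point on a curve already planned. This stands. A reader might infer that the stated uncertainty of the whole cost-utility result is wrong, and the document does not support that.

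A reader might also infer that an ICUR interval can never be interpreted, or that the protocol predicts a saving. Neither holds. The north-east examples give usable intervals, and the Discussion hypothesises cost-effectiveness, with saving only as a hedged possibility.

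The document does not say how the interval will be built, and the percentile method used here is an assumption. An article may leave that detail, and a rule for several quadrants, to a fuller plan, so their absence is not the point. The point is the unconditional promise of a ratio interval. Sign ambiguity and lack of ordering belong to the ratio, so another bootstrap construction would not remove them.

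Finally, the magnitudes depend on chosen inputs. That is true, and they are offered only as illustration.

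**Conclusion.** The point holds in conditional form. The plan commits to a statistic that misleads when replicates span quadrants or the QALY difference is not clearly away from zero, and the protocol's own expectations and its 6-month horizon make that a realistic outcome. The arithmetic on sign and ordering is certain. The likelihood and width of an uninterpretable interval rest on assumed means, SDs and correlation that the document does not supply. The fault is limited to the ICUR interval: the plane, the acceptability curves, the primary HADS analysis and the sample size are unaffected. Severity is minor to moderate.

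**What to change.** Reword the ICUR sentence in the cost-utility analysis. From the same 5000 replicates, report:

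- incremental costs and incremental QALYs, each with a 95% interval;
- the share of replicates in each quadrant, beside the planned plane;
- incremental net monetary benefit with a 95% interval at stated willingness-to-pay thresholds, beside the planned acceptability curves.

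Give an interval for the ICUR only when essentially all replicates lie in one trade-off quadrant (north-east or south-west). Otherwise omit it and state dominance where it applies. The cost is wording and a few more lines of output, with no change to data collection, sample size or the primary analysis.

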## Discussion

This paper describes the protocol of a study that aims to provide evidence on the prevalence of an adjustment disorder among cancer patients and the reach, effectiveness, cost-utility and budget impact of tailored psychological treatment.

The first part of this project aims to investigate the prevalence. As mentioned above, previous studies have found prevalence rates varying between 6 and 19% [5–8]. However, these studies were heterogeneous in terms of cancer type and methodological quality, warranting further research. Also, the conceptualization of adjustment disorder among cancer patients is poorly studied, which may limit the precision of adjustment disorder diagnosis [51]. Most studies used diagnostic interviews to diagnose adjustment disorder [5–8]. Mehnert et al. [7], on the other hand, first screened patients on their level of psychological distress using the patient health questionnaire (score of 9 or higher on the PHQ-9), followed by a diagnostic interview in those patients with increased levels of psychological distress. As it is estimated not to be feasible to conduct a diagnostic interview in the more than 3000 patients needed for this study, we will in line with the study of Mehnert et al. [7] first screen the patients on their risk for having an adjustment diagnosis using patient-reported outcomes measures. As it is not yet clear which screening questionnaire should be used to preselect patients on their risk for having an adjustment disorder [3], we will preselect patients using the DT, problem list and the HADS. Previous studies have investigated the predictive value of the DT [52–54], HADS [53, 55–59], PHQ-2 [52], Zung Self-rating Depression Scale (ZSDS) [60] and One Question Interview (OQI) [54] to identify patients with an adjustment disorder. Most studies, however, have been conducted on the HADS and DT. Three studies that investigated the predictive value of the DT showed that a cut-off ranging between the > 3 and > 5 resulted in the best screening performance, whereas other studies investigating the HADS found a cut-off ranging between > 9 and > 15. In our study all patients with an increased risk on the questionnaire (i.e. HADS score > =11, DT > =4, certain problems on the problem list or wanting to talk to a psychologist or social worker) will be asked to participate in the diagnostic interview. In line with the study of Mehnert et al. [7], we expect to find a prevalence rate of adjustment disorder of 11% (independent of other diagnoses).

The second part of this project aims to investigate the effectiveness, cost-utility and budget impact of the tailored psychological intervention. It is expected that this psychological intervention will be especially effective, since the intervention is tailored to the individual needs regarding intensity of the intervention (i.e. number of modules provided) and wishes regarding the type of intervention. Besides being effective, it is hypothesized that offering this intervention will be cost-effective and potentially even cost-saving.

The cost saving potential is related to the design of the study in which patients are first provided with the short psychological treatment (module 1). The following modules (i.e. module 2 and 3) will only be offered to the patient if the previous psychological treatment module is insufficiently effective. This principle is comparable to a previously investigated stepped care intervention targeting head and neck cancer and lung cancer patients with psychological distress which was shown to be more effective and less costly compared to usual care [17, 27].

### Strengths and limitations

A strength of this study is that its design is in line with clinical practice, as we will investigate a tailored psychological intervention, which may consist of different types of interventions, and not only one specific intervention. Second, this study investigates not only the effectiveness and cost-utility of tailored psychological treatment, but also the prevalence of adjustment disorder and reach of the tailored care. Insight in the prevalence and reach will enable accurate budget impact analysis of providing such psychological treatment to cancer patients with an adjustment disorder. Third, the proposed study will assess the cost-utility and budget impact of the intervention from a healthcare, societal and insurer perspective. So far, the majority of the performed economic evaluations have used the healthcare perspective. However, several guidelines recommend using the societal perspective which includes also for examples productivity losses and informal care costs [61, 62]. This is of importance since these costs have shown to be a great contributor to costs of cancer [63]. Finally, detailed analysis will be conducted on determinants of the prevalence of an adjustment disorder and the reach of psychological care, which will help to identify possible risk groups in the future.

This study, however, also has some limitations. First, this study includes a short follow-up of 6 months in total, which hampers the possibility to investigate the effectiveness and cost-utility of the intervention on the long term. However, a longer waiting list period was considered as not ethical for the patients. Second, the provided intervention consists of a great diversity of evidence-based interventions. Although this approach follows current routine psychological care, it makes it harder to draw conclusions on the effectiveness of any one specific intervention (e.g. self-management or group therapy). Third, this study targets a heterogeneous study population of mixed cancer patients treated with either curative or palliative treatment, which may limit the ability to draw firm conclusions on the effectiveness of psychological treatment in specific study populations. Fourth, as mentioned above a different method will be used to diagnose adjustment disorder compared to methods used in the previous studies, which makes comparison with previous studies harder. However, to investigate the quality of the diagnostic interviews, these interviews will be checked on robustness by audio recording it.

### Implementation and clinical practice

In the Netherlands, psychological treatment for cancer patients undergoing medical treatment is reimbursed as part of the reimbursement of cancer treatment. Since 2012, however, psychological cancer treatment during follow-up (after active cancer treatment) is no longer reimbursed for cancer patients with an adjustment disorder To make an evidence-based decision on future reimbursement of psychological treatment targeting cancer patients with an adjustment disorder, the Dutch minister of Health, Welfare and Sport requested this study on the prevalence of adjustment disorders, actual reach, effectiveness, cost-utility and budget impact of psychological treatment for this patients group. If this study will demonstrate that the psychological intervention is effective and cost-effective, further steps need to be taken to support reimbursement and implementation of this program in clinical practice. In addition, guideline committees will be informed and recommended to adapt the guidelines of tailored psychological care for cancer patients with an adjustment disorder.

## Conclusion

In conclusion, if the psychological intervention is effective and cost-effective, this study will provide support for the reimbursement of psychological interventions for cancer patients with an adjustment disorder. Consequently, this study may contribute to the implementation and optimization of accessibility of psychological treatment for cancer patients with an adjustment disorder. However, considering a broader perspective, this study may also add important knowledge to the literature of economic evaluations of psychological interventions for cancer patients in general.

## Trial status

This study is ongoing. No publications containing the results of this study have been published or submitted to any other journal.

## Data Availability

Full dataset and statistical code will be made available in a repository 3 months after publication of all study outcomes in peer-reviewed journal.

## Abbreviations

CIS: Checklist Individual Strength
DT: distress thermometer
EORTC QLQ-C30: European Organization for Research and Treatment of Cancer Quality of Life Questionnaire
HADS: Hospital Anxiety and Depression Scale
HCP: healthcare professional
iMCQ: Medical consumption questionnaire
iPCQ: Productivity cost questionnaire
MAC: Mental Adjustment to Cancer
MFI: multidimensional fatigue inventory
